### Neuropsychological evaluation, assessment of depression and estimation of premorbid intelligence

Extensive neuropsychological examination includes: global measurements (MMSE) [33], tasks exploring verbal and spatial short-term and long-term memory (Digit and Visuo-spatial Span forward and backward [34], Rey Auditory Verbal Learning Test [35], Short Story Immediate and Delayed Recall [36], Rey-Osterrieth complex figure recall [37]), attention (Trail Making Test A [38], attentional matrices [39], Multiple Features Targets Cancellation [40]), language (Category Fluency Task [41], Phonemic Fluency Task [35] and Italian language battery: Screening for Aphasia NeuroDegeneration [42]), constructional praxis (Copying drawings [35], Rey-Osterrieth complex figure copy [37], Clock test [43]) and executive function (Trail Making Test B [38], Stroop Test [44], Frontal Assessment Battery [45]). The subjective perception of memory impairment will be investigated using the Memory Assessment Clinics-Questionnaire (MAC-Q) [46]. Premorbid intelligence will be estimated using the Short intelligence test (TIB) [47], that has been constructed as the Italian equivalent of the National Adult Reading Test [48]. The presence and severity of depressive symptoms will be evaluated by means of the 22-item Hamilton Depression Rating Scale (HDRS) [49]. Katz Index of Independence in Activities of Daily Living (ADL) [50] scale will be used to assess functional capacities at baseline and at follow-up (Table 1).

**Table 1 Tab1:** Explored cognitive domains and respective neuropsychological tests

Cognitive domains	Neuropsychological tests	References
Global cognition	MiniMental-State Examination (MMSE)	(Magni et al. 1996) [33]
Verbal short-term memory	Digit span forward and backward	(Monaco et al. 2013) [34]
Verbal long-term memory	Rey Auditory Verbal Learning Test (RAVLT)	(Carlesimo, Caltagirone, e Gainotti 1996) [35]
	Short story recall	(De Renzi, Faglioni, e Ruggerini 1977) [36]
Spatial short-term memory	Visuo-spatial span forward and backward	(Monaco et al. 2013) [34]
Spatial long-term memory	Rey-Osterrieth complex figure recall	(P. Caffarra et al. 2002) [37]
Attention	Attentional matrices	(Della Sala et al. 1992) [39]
	Trail Making Test part A	(Giovagnoli et al. 1996) [38]
	Multiple Features Targets Cancellation	(Marra et al. 2013) [40]
Language	Category fluency task	(Novelli et al. 1970) [41]
	Phonemic fluency task	(Carlesimo, Caltagirone, e Gainotti 1996) [35]
	Screening for Aphasia in NeuroDegeneration (SAND)	(Catricalà et al. 2017) [42]
Constructional praxis	Copying drawings	(Carlesimo, Caltagirone, e Gainotti 1996) [35]
	Rey-Osterrieth complex figure copy	(P. Caffarra et al. 2002) [37]
	Clock test	(Shulman et al. 1993) [43]
Executive function	Trail Making Test part B	(Giovagnoli et al. 1996) [38]
	Stroop Test	(Paolo Caffarra et al. 2002) [37, 44]
	Frontal Assessment Battery	(Appollonio et al. 2005) [45]
Perception of memory impairment	Memory Assessment Clinics-Questionnaire (MAC-Q)	(Crook, Feher, e Larrabee 1992) [46]
Premorbid intelligence	Short intelligence test (TIB)	(Colombo et al. 2000) [47]
Depression	Hamilton Depression Rating Scale	(Hamilton 1960) [49]
Functional capacities	Katz Index of Independence in Activities of Daily Living	(Katz et al. 1963) [50]

### Personality traits and leisure activities

We will use the Big Five Factors Questionnaire (BFFQ) [51] to assess personality traits. Participants will be asked to fill out a questionnaire that measures the five factors of: 1) emotional stability, 2) energy, 3) conscientiousness, 4) agreeableness, and 5) openness to culture and experience. The inventory follows a widely accepted five-traits personality model [51, 52]. For the 24 items of each factor, subjects will rate their level of agreement on a five-point scale ranging from strongly agree to strongly disagree. Item scores will be computed for each factor to yield a summary measure of the trait with higher values representing a greater degree of the explored dimension.

At baseline, subjects will be interviewed regarding participation, when they were 30–40 years old, in nine Intellectual Activities, seven Social Activities and seven Physical Activities (modified from Yarnold PR et al. [53]). The frequency of participation will be reported for each activity on a Likert scale ranging from 0 to 5, where 0 refers to never, 1 to occasionally, 2 to monthly, 3 to once a week, 4 to several days per week and 5 to daily.

### EEG and ERP recording

Resting-state EEG data will be collected at the Neurophysiological Laboratory of IRCCS Don Gnocchi (Florence, Italy) using the 64-channel Galileo-NT system (E.B. Neuro S.p.A.). The EEG will be recorded continuously from 64 electrodes using an EEG Prewired Headcaps. Electrodes were positioned according to the 10–10 international system (AF7, AF3, Fp1, Fp2, Af4, Af8, F7, F5, F3, F1, F2, F4, F6, F8, FT7, FC5, FC3, FC1,FC2, FC4, FC6, FT8, T3, C5, C3, C1, C2, C4, C6, T4 TP7, CP5, CP3, CP1, CP2, CP4, CP6, TP8, T5, P5, P3, P1, P2, P4, P6, T6, Fpz, PO7, PO3, O1, O2, PO4, PO8, Oz, AFz, Fz, FCz, Cz, CPz, Pz, and POz). The ground electrode will be placed in front of Fz. Horizontal eye movements will be detected by electrooculogram (EOG). Data will be digitized at a sampling rate of 512 Hz and analogue–digital precision will be 16 bits. The recording will be referenced to the common average of all electrodes, excluding Fp1 and Fp2. Re-referencing will be done prior to the EEG artifact detection and analysis. Electrode–skin impedance will be set below 5 kΩs. Subjects will be seated in a reclined chair in a comfortable position. Resting EEG recording begins with a 10-min eyes-closed registration followed by an alternance of 3 min eyes-open and 3 min eyes closed, repeated twice. Only the eyes-closed portions of the signal will be used for subsequent analyses.

ERP acquisition will be performed with the same EEG system used for EEG data acquisition. The participants will be administered an ERP test battery with concurrently recorded EEG consisting of a 3-choice vigilance task (3CVT) and standard image recognition task (SIR).

In order to remove electrophysiological and non-electrophysiological artifacts from the raw signals, we will apply a custom preprocessing pipeline written in MATLAB with the use of the EEGLAB toolbox functions [54]. The pipeline consists of two main steps: the PREP pipeline [55], followed by independent component analysis (ICA) to remove artefactual components [56]. Moreover, to generate the ERP epochs, time windows from -300 ms to + 1000 ms will be created for each EEG recording channel, with the stimulus presentation centred at 0 ms and the average of the trials from each epoch will be calculated.

### Blood sample collection and analysis of *APOE* and *BDNF* genes

Blood samples will be collected by venipuncture into standard polypropylene EDTA test tubes (Sarstedt, Nümbrecht, Germany) at the Neurology Unit of Careggi University Hospital. They will be centrifuged within two hours at 1300 rcf at room temperature for 10 min, and plasma will be isolated and stored at -80 °C until tested at the Laboratory of Neurogenetics at Careggi University Hospital.

*APOE* genotypes will be investigated by HRMA. The samples with known *APOE* genotypes, which had been validated by DNA sequencing, will be used as standard references.

Analysis of *BDNF* rs6265 polymorphism will be performed using HRMA and the genotypes will be identified through Sanger sequencing (SeqStudio Genetic Analyzer, ThermoFisher).

### CSF collection and AD biomarker measurement

CSF samples will be collected at 8:00 a.m. by lumbar puncture at the Neurology Unit of Careggi University Hospital. Samples will be immediately centrifuged and stored at -80 °C until performing the analysis at the Laboratory of Neurogenetics of Careggi University Hospital. Aβ_42_, Aβ_40_, t-tau, and p-tau will be measured using a chemiluminescent enzyme immunoassay (CLEIA) analyser LUMIPULSE G600 (Fujirebio, Tokyo, Japan). Cut-off values for CSF biomarkers will be determined following Fujirebio guidelines (diagnostic sensitivity and specificity using clinical diagnosis and the follow-up golden standard as of November 19^th^, 2018).

### Data collection and management

Data collection will be carried out anonymously on REDCap, an online-based software for the design of databases. Data will be collected in a pseudo-anonymized way, attributing a record ID to each patient on the electronic database and saving the correspondence between names and identification codes on a separate document.

### EEG pre-processing

The EEG preprocessing will be conducted following the methodology outlined in Lassi et al., 2023 [57]. Firstly, the PREP pipeline will be applied, which involves high-pass filtering the signals at 1 Hz, removing line noise using the CleanLine routine, and identifying noisy channels through a combination of methods. Following the interpolation of noisy channels, the data will be re-referenced to the median. Subsequently, Independent Component Analysis (ICA) [58] will be performed on the re-referenced signals to eliminate artifacts while preserving neural components. To classify the components as neural or artefactual, a semi-automated process will be employed, utilizing both the ICLabel [59] toolbox and visual inspection. After completing these two processing steps, a final visual inspection will be conducted to identify and remove any remaining artifacts, if present.

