The final statistical analysis will involve extracting microstate maps [61] for each subject individually. Initially, a set of common microstates will be extracted from all subjects, regardless of conditions, using the modified k-means algorithm [62]. Then, individual microstate maps will be generated, and the template maps will be matched with the previously obtained grand-averages. The EEG signals of each subject will be reconstructed as a sequence of microstates by assigning each topography to the most similar microstate average map. From the reconstructed microstate sequence, various metrics such as duration, transition probability, and complexity of the sequence will be used as features. Spectral features, network metrics, and microstate features will be compared across conditions, providing the foundation for the machine learning analysis.

Regarding the ERP data, both spectral features (like the EEG processing) and voltage-level signals (amplitude, latency, integral of the signal) from different phases of the ERP will be used as input features.

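### As written, a 1 Hz high-pass precedes extraction of ERP amplitude and integral, which would attenuate slow late components by an amount that depends on wave width and an unstated filter design

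*Protocol article*

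**What the plan says.** Three sections of the protocol article bear on this.

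- **EEG and ERP recording.** ERP and resting EEG share one recording system: "ERP acquisition will be performed with the same EEG system used for EEG data acquisition". A single custom MATLAB pipeline then cleans the raw signals: "The pipeline consists of two main steps: the PREP pipeline [55], followed by independent component analysis (ICA", the quote ending inside the abbreviation. The next sentence turns to the ERP data: "to generate the ERP epochs, time windows from -300 ms to + 1000 ms will be created". Sampling is at 512 Hz.
- **EEG pre-processing.** This section spells out the PREP step, "which involves high-pass filtering the signals at 1 Hz, removing line noise using the CleanLine routine", followed by noisy-channel interpolation and re-referencing. ICA is run on the re-referenced signals.
- **EEG Statistical analysis.** Besides spectral ERP features, "voltage-level signals (amplitude, latency, integral of the signal) from different phases of the ERP will be used as input features".

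The article gives no second cut-off for ERP data and no return to less-filtered data after ICA. It does not state the filter type, order or phase, or whether 1 Hz is the pass-band edge or the half-amplitude point. It names no ERP component or measurement window.

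**The concern.** A 1 Hz high-pass suits the resting-state analysis, whose lowest band starts at 1 Hz. It suits slow evoked waves less well. A late deflection lasting several hundred milliseconds carries much of its content below 1-2 Hz, and the filter removes part of it and adds opposite-sign lobes on either side. The peak shrinks, and the area under the wave shrinks more. Because the loss grows with duration, two patients with the same true amplitude but different wave widths receive different amplitude values.

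ERP is one of the additions the study makes to its earlier predictors (Background), and the Discussion says it has not been studied in SCD so far. At stake is how much information the ERP features carry into the model, and whether amplitude can be read as amplitude.

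**Working it through.** The plan gives no figure on this point, so there is none to reproduce. The check estimates how large the attenuation would be.

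**Inputs from the article.** High-pass at 1 Hz; sampling at 512 Hz; epoch -300 to +1000 ms; features amplitude, latency and integral.

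**Assumptions.** Unit Gaussian waves of SD 80, 120 and 200 ms, peaking at 400, 500 and 600 ms. Two readings of the filter:
- FIR: zero-phase Hamming windowed-sinc, pass-band edge 1 Hz, so -6 dB at 0.5 Hz.
- Butterworth: second order, cut-off 1 Hz, run forward and backward.

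**Step 1: expected size by formula.** A Gaussian wave of SD s has a spectrum proportional to exp(-2π²f²s²). The share of its peak that comes from frequencies below c is erf(√2·π·c·s).
- c = 0.5 Hz (FIR half-amplitude point): erf(0.178) = 0.20, erf(0.267) = 0.29, erf(0.444) = 0.47.
- c = 1 Hz: erf(0.355) = 0.38, erf(0.533) = 0.55, erf(0.889) = 0.79.

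The simulated peak losses without baseline correction are 20%, 29% and 46% (FIR) and 41%, 56% and 77% (Butterworth), close to these values.

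**Step 2: with baseline correction on -300 to 0 ms.** The article does not mention this correction. It is applied to both cut-offs so that they are compared on equal terms. The half-height window is the interval in which the unfiltered wave exceeds half its peak.

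| Filter | Wave SD | Peak lost | Half-height integral lost | 0-1 s integral lost |
|---|---|---|---|---|
| FIR, 1 Hz | 80 ms | 11% | 13% | 35% |
| FIR, 1 Hz | 120 ms | 19% | 23% | 48% |
| FIR, 1 Hz | 200 ms | 34% | 40% | 54% |
| Butterworth, 1 Hz | 80 ms | 40% | 47% | 99% |
| Butterworth, 1 Hz | 120 ms | 57% | 66% | over 100% (sign reverses) |
| Butterworth, 1 Hz | 200 ms | 77% | 85% | about 100% |
| FIR or Butterworth, 0.1 Hz | 80-200 ms | 0-1% | 0-1% | 0-2% |

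The 0-1 s integral falls most because a high-pass removes the zero-frequency content, which is the total area: within a long window the side lobes offset the wave.

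**Step 3: mixing of amplitude with duration.** Take two waves of equal true peak, SD 80 and 200 ms. Under the FIR they keep 89% and 66%, so the broad one reads 0.66/0.89 = 0.74 of the narrow one. Under the Butterworth they keep 60% and 23%, a ratio of 0.38.

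**Step 4: where the effect is small.** For a component of 50 ms full width at half maximum, designs with the cut-off at 1 Hz keep 79-96% of the peak, and the FIR with its edge at 1 Hz keeps 95-99%.

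**Step 5: latency.** Zero-phase filters leave the peak time unshifted. Causal Butterworth filters (orders 1 and 2) move the peaks of 150-500 ms wide components about 18-196 ms earlier. The article does not say which kind is used.

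**The case against.** **ERP data may not pass through this step.** The section with the 1 Hz filter is headed for EEG and never mentions ERP, it follows a cited methodology, and a condensed article may leave an ERP-specific setting to a fuller document. This stands in part: that ERP data pass through the filter is an inference. It is a strong one, because the joint EEG and ERP section gives a single pipeline for the raw signals and then cuts the ERP epochs. The point also does not rest on silence alone, since the article itself fixes the cut-off and the order of steps.

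**The integral is taken over phases of the ERP, not over the whole epoch.** This stands. The near-total loss over 0-1 s applies to a window the article does not specify, so the half-height figures are the fairer guide.

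**Attenuation is not loss of ranking.** This stands too. In a simulation of 1,500 assumed patients (amplitude mean 5, SD 2; wave SD 80-200 ms; peak 400-600 ms), filtered and unfiltered 300-800 ms integrals correlated 0.98 (FIR) and 0.95 (Butterworth). Filtered peak against true amplitude correlated 0.96 and 0.83. A reader might infer that the ERP features become close to uninformative, or that a null ERP result would be a filter artefact. The documents do not support either. Only the Butterworth integral over 0-1 s fell to a correlation of about 0, and every participant gets the same filter.

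**ERP is one of several feature families and is subject to feature selection.** True, and it limits the consequence for the study as a whole. It does not justify feeding distorted ERP features into that selection when the remedy is cheap.

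**Conclusion.** The point holds in a limited form. Taken together, the three sections put a 1 Hz high-pass ahead of ERP amplitude and integral, with no separate ERP branch. For slow late components (assumed Gaussian, SD 80-200 ms, baseline-corrected), the loss runs from 11-34% of the peak and 13-40% of the half-height integral under the milder FIR reading to 40-77% and 47-85% under the Butterworth reading. At 0.1 Hz it is about 0-2%.

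The result rests on three things the article does not state: that ERP data go through this filter, the filter design, and the width of the components that will be measured. If only narrow early components are used, the effect is small. The harm is weakened predictive information and an amplitude feature that partly reflects wave duration. No bias between progressors and non-progressors is shown. The change is worth making before the ERP features are extracted, but it does not threaten the study.

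**What to change.** State in the plan which signal the ERP epochs are cut from, and give the filter type, order, phase and definition of the cut-off. If they are cut from the 1 Hz signal, use two copies:

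1. Keep the 1 Hz copy for line-noise removal, bad-channel detection, estimation of the ICA weights and the resting-state analysis.
2. Apply the resulting ICA weights and channel interpolation to a second copy high-passed at a lower cut-off, for example 0.1 Hz.
3. Baseline-correct the epochs of that copy on -300 to 0 ms and take ERP amplitude, latency and integral from it.

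The cost is one extra branch in the existing scripts. No new recordings are needed, stored raw data can be reprocessed, and the resting-state results do not change. The drawback is more slow drift in the second copy, so a few more ERP trials may be rejected.

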### EEG Statistical analysis

Firstly, we will calculate the power spectral density (PSD) of the signal recorded in each channel using the Welch's method. The PSD will be computed on continuous windows of EEG signals, applying Hanning windows with no overlap. The spectrum will be divided into four canonical frequency bands: delta (1–4 Hz), theta (4–8 Hz), alpha (8–13 Hz), and beta (13–30 Hz). The scalp will be divided into six regions of interest (ROIs): frontal right (Fp2, AF4, AF8, F2, F4, F6, F8), frontal left (Fp1, AF3, AF7, F1, F3, F5, F7), central right (FC2, FC4, FC6, FT8, C2, C4, C6, T4, CP2, CP4, CP6), central left (FC1, FC3, FC5, FT7, C1, C3, C5, T3, CP1, CP3, CP5), occipital right (P2, P4, P6, T6, PO8, PO4, O2), and occipital left (P1, P3, P5, T5, PO7, PO3, O1). ROI power will be computed as the average relative power from channels belonging to each ROI.

Next, we will analyse the connectivity between pairs of ROIs using LORETA source-reconstructed signals and extract several network metrics from the weighted undirected adjacency matrices. These metrics will include the average strength of connectivity among pairs of ROIs (mean weight of non-zero connections), the weighted clustering coefficient (C) and the weighted characteristic path length (L) [60]. Finally, we will compute the small-world coefficient [57]:$$\Omega = \frac{Lr}{L}- \frac{C}{Cl}$$where L and C are the previously computed weighted clustering coefficient and weighted characteristic path length, whereas Lr is the weighted characteristic path length of an equivalent random network and Cl is the weighted clustering coefficient of an equivalent lattice network.

The final statistical analysis will involve extracting microstate maps [61] for each subject individually. Initially, a set of common microstates will be extracted from all subjects, regardless of conditions, using the modified k-means algorithm [62]. Then, individual microstate maps will be generated, and the template maps will be matched with the previously obtained grand-averages. The EEG signals of each subject will be reconstructed as a sequence of microstates by assigning each topography to the most similar microstate average map. From the reconstructed microstate sequence, various metrics such as duration, transition probability, and complexity of the sequence will be used as features. Spectral features, network metrics, and microstate features will be compared across conditions, providing the foundation for the machine learning analysis.

Regarding the ERP data, both spectral features (like the EEG processing) and voltage-level signals (amplitude, latency, integral of the signal) from different phases of the ERP will be used as input features.

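### ROIs are defined only as six scalp electrode groups, yet serve as nodes for LORETA source connectivity; carried over as six nodes, the small-world coefficient Ω loses its usual meaning

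*Protocol article*

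**What the plan says.** All of this is in the protocol article, section EEG Statistical analysis.

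- The first paragraph defines the regions: "The scalp will be divided into six regions of interest (ROIs"), followed by six electrode lists. Their stated use is spectral: "ROI power will be computed as the average relative power from channels belonging to each ROI".
- The next paragraph will "analyse the connectivity between pairs of ROIs using LORETA source-reconstructed signals and extract several network metrics" "from the weighted undirected adjacency matrices". The metrics are average strength ("mean weight of non-zero connections"), the clustering coefficient C, the path length L, and Ω = Lr/L − C/Cl.
- The references in Ω are given as: "Lr is the weighted characteristic path length of an equivalent random network and Cl is the weighted clustering coefficient of an equivalent lattice network".
- The line under the formula reads "where L and C are the previously computed weighted clustering coefficient and weighted characteristic path length". This reverses the sentence before it, where C is clustering and L is path length.
- On use: "Spectral features, network metrics, and microstate features will be compared across conditions, providing the foundation for the machine learning analysis".

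The article gives no second set of ROIs, no atlas or parcellation, no node count, and no density or threshold for the matrices.

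**The concern.** The same term is used for two different objects. A set of scalp channels is a valid unit for averaging relative power. It is not a region in which a LORETA source signal can be located. An analyst must therefore either supply an unstated parcellation or carry the six ROIs over as network nodes.

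The second choice matters for Ω. A lattice should have C close to Cl and L above Lr, so Ω is negative. A random network should have L close to Lr and C below Cl, so Ω is positive. A small-world network should lie between, near zero. With very few nodes the random and lattice references hardly differ from the network itself, and this ordering can fail. Ω would then enter the group comparisons and the candidate features with a label that does not describe what it measures. A difference, or the lack of one, could be misread as a finding about network organisation in early disease.

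**Working it through.** **1. Node count.** The six lists hold 7, 7, 11, 11, 7 and 7 channels, which is 50 of the 61 electrodes named under EEG and ERP recording. Six nodes give 6 × 5 / 2 = 15 pairs.

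**2. Exact unweighted case, 12 of 15 edges (ring lattice of degree 4).**
- Three edges are missing, so there are 15 × 14 × 13 / 6 = 455 possible graphs.
- An unconnected pair has four possible common neighbours. The two other missing edges cannot remove all four, so every distance is 1 or 2.
- Hence L = (12 × 1 + 3 × 2) / 15 = 1.2 for all 455 graphs. Lr/L is always 1, and the path term carries no information.
- The ring lattice has C = 0.667, the lowest of all 455. The mean over all graphs is 0.80 and the maximum is 0.90.
- Lattice: Ω = 1 − 0.667/0.667 = 0. Random, on average: Ω = 1 − 0.80/0.667 = −0.20. Extreme: 1 − 0.90/0.667 = −0.35. Random networks fall below the lattice, which is the reverse of the intended order.
- With 6 edges (ring of degree 2) Cl = 0, so Ω is undefined.

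**3. Weighted case, which is what the plan specifies.** The document gives no weight distribution, density or null model, so these are assumptions:
- uniform, beta or lognormal weights;
- density 1.0, 0.8 or 0.6;
- random references with shuffled weights and a ring-ordered lattice reference;
- small-world networks made by reshuffling 15% of a lattice.

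There were 150 replicates at 6 nodes and 40 at 20 nodes. The AUC is the chance that the type expected to have the higher Ω does have it: 0.5 is no separation, 1 is complete separation in the expected order, and values near 0 are separation in reverse.

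| Weights | Density | 6 nodes: small-world vs lattice | 6 nodes: random vs lattice | 20 nodes: both contrasts |
|---|---|---|---|---|
| uniform | 1.0 | 0.49 | 0.40 | 1.00, 1.00 |
| uniform | 0.8 | 0.43 | 0.06 | 0.99, 1.00 |
| uniform | 0.6 | 0.45 | 0.34 | 1.00, 1.00 |
| beta | 1.0 | 0.49 | 0.43 | 1.00, 1.00 |
| beta | 0.8 | 0.46 | 0.06 | 1.00, 1.00 |
| beta | 0.6 | 0.44 | 0.39 | 1.00, 1.00 |
| lognormal | 1.0 | 0.45 | 0.24 | 1.00, 1.00 |
| lognormal | 0.8 | 0.39 | 0.08 | 1.00, 1.00 |
| lognormal | 0.6 | 0.49 | 0.36 | 1.00, 1.00 |

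A further run at density 0.5 with uniform weights gave 0.52 and 0.48 at 6 nodes. The six-node ranges are therefore 0.39 to 0.52 and 0.06 to 0.48.

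**4. More nodes.** With 64 nodes, full density and uniform weights, mean Ω is −0.181 for lattice, −0.057 for small-world and 0.004 for random, with AUC 1.0 for every pair. The corresponding six-node means with full uniform weights are 0.001, −0.002 and −0.015, with SDs of 0.024, 0.023 and 0.044. The failure comes from the node count, not from the formula.

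**The case against.** The strongest reply is that the authors never meant six nodes. The scalp groups are tied explicitly to spectral power, and a new paragraph then turns to source signals, where such groups make no sense. The parcellation may well be in the full protocol or in the cited methods, and a journal article commonly leaves such detail there. This stands in part: the six-node network is the literal reading, not a certain one. But the article does more than omit a detail. It defines the term channel by channel and reuses it for something the definition does not fit, and neither citation in that paragraph is given as the source of the ROIs.

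A second reply is that the machine learning section applies feature selection, which can discard a useless Ω. That limits the harm to prediction. It does not help the group comparisons, and a feature with reversed sign may be kept and then misinterpreted.

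A reader might also infer more than the documents support:
- **That Ω would be zero for every patient.** This holds only if a complete graph is rewired with its weights left in place. With shuffled weights Ω scatters around zero, and zero edges are not excluded.
- **That Ω at six nodes carries no information.** Near 80% density it separates random from lattice strongly, in the wrong direction. A classifier could use that; the usual interpretation could not.
- **That C, L and mean strength fail too.** Only Ω was tested. The others can be computed on six nodes as coarse summaries.
- **That the swapped symbols would corrupt Ω.** The preceding sentence and the definitions of Lr and Cl make the intended meaning clear, so this is a wording slip.

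**Conclusion.** The point holds in a limited form. The section defines ROIs only as scalp electrode groups and uses them, without redefinition, as nodes for source connectivity. If followed as written, the network has 6 nodes and 15 edges. Ω then does not separate lattice from small-world (AUC 0.39 to 0.52), and where it separates random from lattice it does so with reversed sign (AUC 0.06 to 0.48). At 20 and 64 nodes the order is correct.

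The exact unweighted result needs no distributional assumption. The weighted results rest on assumed weight models, densities, rewiring share and reference networks, but the conclusion was the same across all those tried. If the authors already use a parcellation of adequate size, what remains is to state it. The effect is confined to one feature within the network family, and neither the sample size nor the outcome definitions are touched.

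**What to change.** 1. Keep the six scalp ROIs for spectral power only.
2. For connectivity, name the source-space parcellation and its number of nodes, about 20 or more, and compute Ω on that. Twenty is a size at which Ω worked in the simulations, not a proven minimum. The team should also justify that its montage supports the number chosen.
3. If connectivity stays at six ROIs, drop Ω and use the 15 pairwise connectivity values. Mean strength, C and L may be kept, described as coarse summaries.
4. Under the formula, state that L is the characteristic path length and C the clustering coefficient.

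The cost is wording plus computation on recordings that are already planned; no new recording is needed. The downside of item 2 is that a parcellation must be chosen and source leakage between neighbouring parcels must be handled in the connectivity measure.
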